#### Predefined subgroup analysis

2.12.6

Subgroup analyses will be prespecified in accordance with subgroup data reporting guidelines (49), with details provided in Table 5 (50–54). The results, which will be Bonferroni-corrected for multiple comparisons, will be reported as secondary exploratory outcomes. Treatment effect differences between the acupuncture and rehabilitation control groups across subgroups will be presented using forest plots.

**TABLE 5 T5:** Predefined subgroup categories and rationale.

Subgroup category	Stratification basis (determined at baseline)	Theoretical rationale
Baseline FOIS score subgroup	Low-level group (FOIS = 2), Medium-level group (FOIS = 3–4)	The severity of baseline swallowing function may affect intervention response. Patients with FOIS = 2 and those with FOIS = 3–4 have different therapeutic goals (e.g., prioritizing “oral feeding safety” for FOIS = 2 vs. “feeding independence” for FOIS = 3–4) (50).
Stroke subtype subgroup	Cortical infarction group, subcortical infarction group	Different infarction locations cause varying degrees of damage to the swallowing neural circuit: cortical infarction primarily impairs the cortical swallowing center, while subcortical infarction affects the cortico-brainstem pathway, which may lead to differences in the regulatory effect of acupuncture (51).
Age subgroup	Young group (18–60 years), Elderly group ( > 60 years)	Elderly patients often exhibit atrophy of swallowing muscles. This anatomical change may result in a slower response to the “neuroregulatory effect” of acupuncture compared to young patients (52).
Baseline NIHSS score subgroup	Mild neurological deficit group (NIHSS ≤ 8), moderate neurological deficit group (NIHSS = 9–16)	Stroke severity is correlated with the prognosis of dysphagia. Patients with moderate neurological deficits may require a higher intensity of intervention to achieve meaningful improvements in swallowing function (53).
Deqi adequacy subgroup (acupuncture group only)	Adequate Deqi group (DQI ≥ 4 and ≥ 2 typical sensations with score ≥ 3), inadequate Deqi group (participants who fail to meet the above criteria)	Deqi is a key link in the efficacy of acupuncture. Adequate Deqi (characterized by typical sensations such as soreness, numbness, distension, and heaviness) may enhance the activation of the swallowing neural circuit, thereby strengthening the therapeutic effect of acupuncture (54).

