### Sample size, randomization, and blinding

2.7

The primary efficacy outcome is the FOIS score. As neither our team nor previous studies have used this measure to assess acupuncture efficacy for post-stroke dysphagia, it is not possible to determine an appropriate effect size from existing data. A review of similar studies has revealed that after 4 weeks, the FOIS score difference from baseline was 1.31 (rehabilitation training group) vs. 0.31 (sham training group), with a standard deviation of 1.09 (16). This value will be used as the expected effect size for this trial, and sample size calculations will be conducted based on a superiority trial design (17). These parameters (μA = 1.31, μB = 0.31, σ = 1.09, α = 0.05, power = 0.8, δ = 0.39) were applied in a superiority design with 1:1 allocation. After calculation, nA = nB = 40. Considering a 20% dropout rate, this study is expected to enroll 100 patients.

Randomization will use computer-generated numbers to allocate patients equally to acupuncture or rehabilitation groups. A stratified block randomization design will be employed. An independent statistician will generate all random sequences in SPSS 25.0, with study center and baseline FOIS as stratification factors, block lengths of 4 and 6 randomly interleaved, and the seed number set to 20240420. Allocation concealment will be implemented through sequentially numbered, opaque, sealed envelopes kept by a research coordinator who has no conflicts of interest with the study team. After participants have completed baseline assessments and provided written informed consent, the responsible physician will open the corresponding envelope on-site to reveal the allocation. The statistician generating the random sequence will operate independently of the coordinator handling allocation concealment. Neither patients nor physicians will know the allocation in advance. All participants will be followed for 90 days.

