**FIGURE 2 F2:**
[figure not shown]
Location of acupuncture points (Source: Atlas of meridians and acupuncture points by JiuDaifu).

**TABLE 2 T2:** Anatomical location of selected acupoints.

Acupoints	Location
GB20 (Fengchi)	In the posterior region of the neck, under the occiput, in the depression between the upper part of the sternocleidomastoid muscle and the upper part of the trapezius muscle.
GB12 (Wangu)	On the neck, at the posterior and inferior depression of the mastoid process behind the ear.
TE17 (Yifeng)	On the neck, behind the earlobe, at the anterior and inferior depression of the mastoid process.
CV23 (Lianquan)	In the anterior region of the neck, on the anterior median line, above the laryngeal prominence, and in the depression of the upper edge of the hyoid bone.

Patients will lie in a supine position. GB20 (Fengchi) needles will be bilaterally inserted at a 30° inferior angle toward the thyroid cartilage to a depth of 2.5–3.0 cun (≈65–75 mm). Small-amplitude, high-frequency twisting manipulation will be applied for 1 min to achieve strong stimulation, targeting a throat numbness/swelling sensation called “deqi.” GB12 (Wangu) and TE17 (Yifeng) will be needled with the same depth, angle, and technique as GB20. CV23 (Lianquan) will be inserted to 1.0–1.5 cun (≈25–40 mm) with lifting-thrusting manipulation. All needles will be retained for 30 min. Participants will receive three sessions per week for four consecutive weeks.

Deqi will be assessed subjectively using the Chinese version of the Massachusetts General Hospital Acupuncture Sensation Scale (c-MASS) (20), which evaluates 12 distinct sensations to quantify deqi intensity and quality. Participants will self-complete the c-MASS within 30 s after each needle manipulation. In accordance with prior domestic research (21), “adequate deqi” will be defined as a total c-MASS score ≥ 4, accompanied by at least two typical sensations (soreness, numbness, fullness, or heaviness) each rated ≥ 3. Cases not fulfilling both criteria will be classified as “inadequate deqi.” The Deqi Quality Index (DQI) for each participant will be calculated as the mean of the total c-MASS scores recorded at three time points: initiation of intervention, 15 and 30 min.

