#### The rehabilitation control group

2.8.2

The rehabilitation control group will receive swallowing rehabilitation training three sessions per week under the guidance of professionals, with specific operations as follows:

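### Table 5 lists deqi adequacy as a baseline subgroup, but it arises after randomisation and only in the acupuncture arm, and the plan does not keep it off the between-arm forest plot

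*Protocol article*

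**What the plan says.** Section 2.12.6 of the protocol article announces prespecified subgroups, with details in Table 5. Results are to be Bonferroni-corrected and reported as secondary and exploratory. It then says: "Treatment effect differences between the acupuncture and rehabilitation control groups across subgroups will be presented using forest plots".

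Table 5 has one column defining all the subgroups, headed "Stratification basis (determined at baseline"). Five families stand under it: baseline FOIS, stroke subtype, age, baseline NIHSS, and a fifth labelled "Deqi adequacy subgroup (acupuncture group only"). The fifth is defined as "Adequate Deqi group (DQI ≥ 4 and ≥ 2 typical sensations with score ≥ 3"), against patients who do not meet those criteria. Its rationale says that adequate deqi may strengthen the effect of acupuncture.

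Section 2.8.1 says how deqi is measured: "Participants will self-complete the c-MASS within 30 s after each needle manipulation". The Deqi Quality Index (DQI) is the mean of the c-MASS totals "recorded at three time points: initiation of intervention, 15 and 30 min".

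Section 2.7 fixes the order of events: "After participants have completed baseline assessments and provided written informed consent, the responsible physician will open the corresponding envelope on-site". Section 2.8.2 gives the comparator: "The rehabilitation control group will receive swallowing rehabilitation training three sessions per week under the guidance of professionals".

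Section 2.12.4 separately plans group comparisons of adequate with inadequate deqi.

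**The concern.** A subgroup contrast keeps the protection of randomisation only if membership is fixed before allocation and can be determined in both arms. The first four families in Table 5 are defined by characteristics present before treatment. Deqi adequacy fails on both counts, yet it sits under the same heading and is covered by the same forest-plot sentence.

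The risk is one of interpretation. Deqi here is a patient's report of sensation. The NIHSS items in section 2.9.2.3 include sensory function and language, and the NIHSS row of Table 5 says that stroke severity is related to the outlook for dysphagia. Patients who can feel and report deqi might therefore be those more likely to recover anyway. The documents do not show that this happens, but they make it plausible. An apparent advantage in the adequate-deqi group could then appear with no treatment effect at all, and it would match the rationale already written in the table.

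**Working it through.** **Step 1: timing and availability.**

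| Question | Source | Answer |
|---|---|---|
| When is the subgroup said to be fixed? | Table 5, column heading | At baseline |
| When is c-MASS completed? | 2.8.1 | After needle manipulation; DQI from start, 15 and 30 min |
| When is allocation revealed? | 2.7 | After baseline assessments |
| When does needling occur? | Table 4 | In the treatment weeks; randomisation is in the pre-treatment column |
| Who has a DQI? | 2.8.1, 2.8.2 | Acupuncture patients only; controls are not needled |

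Deqi status is therefore post-randomisation and exists in one arm. The baseline label is wrong on any reading.

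**Step 2: what could be plotted.** A between-arm difference needs patients from both arms in the stratum. No control patient is in either deqi stratum, so the only available between-arm figure sets a subset of needled patients against the whole rehabilitation arm.

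**Step 3: inputs for an illustration.** The SD of 1.09 and the 40 per arm come from section 2.7. The 40 reproduces with a one-sided α of 0.05 (the article does not state sidedness), power 0.80 and net difference 1.31 − 0.31 − 0.39 = 0.61:

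n = 2 × (1.645 + 0.842)² × (1.09 / 0.61)² ≈ 39.5, so 40 per arm; 40 / 0.80 = 50 per arm, 100 in total.

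This figure is not in dispute; it only sets the scale. Three inputs are assumed: no treatment effect, half of the acupuncture arm adequate, and a correlation r of 0.2 to 0.4 between the tendency to deqi and FOIS change.

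**Step 4: spurious difference.** If the upper half of a normal deqi score is adequate, the mean of that half lies 0.80 SD above the overall mean. So:

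- adequate minus all controls = r × 1.09 × 0.80
- adequate minus inadequate (within arm) = twice that

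| r | Adequate vs all controls | Adequate vs inadequate |
|---|---|---|
| 0.2 | 0.17 | 0.35 |
| 0.3 | 0.26 | 0.52 |
| 0.4 | 0.35 | 0.70 |

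A simulation of 6,000 runs per setting gave 0.18, 0.26 and 0.34 for the first contrast.

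**Step 5: false-positive rate.** With 20 adequate patients against 40 controls, SE = 1.09 × √(1/20 + 1/40) ≈ 0.30. The shifts are then about 0.58, 0.87 and 1.17 SE. At a two-sided 5% level the normal approximation gives about 9%, 14% and 21%; simulation gave 9%, 13% and 21%, and 5% at r = 0. Within the arm, at r = 0.3, simulation gave about 32%.

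**Step 6: sensitivity to the adequate share.** At r = 0.3, with 30% to 70% of the arm adequate, the spurious difference from all controls runs from 0.38 down to 0.16. For scale, the margin in section 2.7 is 0.39.

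**The case against.** The strongest reply is that the plan nowhere says it will compare adequate-deqi patients with the rehabilitation arm. A reader might infer this from the forest-plot sentence, but the documents do not establish it. The row is marked as acupuncture only, a one-arm row has no between-arm difference to plot, and section 2.12.4 already gives the adequate-versus-inadequate comparison its own place. On that reading the label is itself the exemption. This stands: the between-arm contrast is one possible reading, and the figures for it only illustrate what would follow.

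It does not dispose of the point. The baseline heading remains wrong, and the forest-plot sentence does not say that one of the five rows is left out. The within-arm comparison is not randomised either, section 2.12.4 does not say so, and its spurious gap is the larger of the two.

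A second reply is that subgroup results are exploratory and Bonferroni-corrected, and that the bias needs a correlation that the documents do not give. Both are true. Exploratory status limits the consequence, and at r = 0 there is no bias. But Bonferroni deals with multiplicity, not with selection: at a 1% level (0.05 over five families, the divisor being assumed) the simulated false-positive rate for the between-arm contrast is still about 2% to 7%.

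**Conclusion.** The point holds as a mislabelled subgroup and an unresolved conflict of wording. Deqi adequacy is not a baseline subgroup and has no counterpart in the control arm. The forest-plot sentence and the acupuncture-only label need to be reconciled.

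The size is conditional. With no treatment effect, half the arm adequate and r between 0.2 and 0.4, plotting the adequate subset against control would carry a bias of about 0.17 to 0.35 FOIS points and a false-positive rate of about 9% to 21%. The within-arm gap would be about 0.35 to 0.70 points. The correlation and the share are assumptions; the flaw in timing and comparator does not depend on them.

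It would go too far to conclude that the trial's subgroup analysis as a whole is invalid, or that the primary comparison is affected by this row. The first four families are not touched by this point, and subgroup results are declared exploratory. Severity is minor to moderate.

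**What to change.** In Table 5, remove the deqi row from the subgroups described as fixed at baseline. In section 2.12.6, state that the acupuncture-versus-rehabilitation forest plot shows only the four baseline families. In section 2.12.4, describe the deqi comparison as an exploratory, non-randomised, post-treatment association within the acupuncture arm, adjusted for baseline prognostic variables already collected, such as FOIS, NIHSS and age.

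This needs changes of wording only, with no new data or patients. What is given up is any between-arm or causal claim for the adequate-deqi subset, which the design cannot support.

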## Discussion

3

As a traditional Chinese medical therapy, acupuncture has gained substantial attention for its therapeutic efficacy and mechanistic potential in the rehabilitation of post-stroke dysphagia, with a well-established theoretical foundation. Current evidence from published studies (55–58) demonstrates promising clinical outcomes associated with acupuncture therapy. However, comparative studies evaluating acupuncture versus conventional swallowing rehabilitation training remain limited in both quantity and methodological rigor. Notably, swallowing rehabilitation training represents the internationally recognized gold-standard treatment for post-stroke dysphagia and has been extensively implemented in clinical practice worldwide. To more precisely elucidate the comparative efficacy between acupuncture and standard rehabilitation therapy, future clinical investigations should incorporate rigorous methodological designs, including standardized outcome measures, robust data collection and analytical approaches, and quantitative characterization of acupuncture parameters, thereby enhancing the overall quality and reliability of research findings.

The acupoint selection in this study—comprising bilateral Fengchi (GB20), Wangu (GB12), Yifeng (TE17), and Lianquan (CV23)—was based on classical acupuncture theory and contemporary clinical evidence supporting their efficacy in dysphagia management. These acupoints are recognized for regulating “Tong Guan Li Qiao” (orifice-opening functions). Neuroanatomically, Fengchi (GB20) is located in the posterior cervical triangle, where the occipital artery and vein anastomose with their branches, and the greater occipital nerve emerges. Deep needling toward the pharynx stimulates the vagus (CN X), glossopharyngeal (CN IX), facial (CN VII), and hypoglossal (CN XII) nerves, enhancing vertebrobasilar arterial circulation (59). Wangu (GB12) and Yifeng (TE17) demonstrate particular clinical relevance for post-stroke dysphagia, with controlled trials confirming that deep needling improves swallowing function in pseudobulbar palsy (60). Anatomically, Wangu (GB12) resides in the depression posterior-inferior to the mastoid process, adjacent to glossopharyngeal (IX), accessory (XI), vagus (X), and hypoglossal (XII) nerve pathways, potentially facilitating sensory afferent transmission to the CNS. Yifeng (TE17) lies near the glossopharyngeal (IX), hypoglossal (XII), and vagus (X) nerves, enabling direct modulation of peripheral neural activity to influence upper motor neuron pathways. Lianquan (CV23) is positioned between the thyroid cartilage and hyoid bone, with the epiglottis deep to this region and the laryngeal inlet inferiorly. This area is innervated by vagus (X) and glossopharyngeal (IX) nerve terminals; acupuncture here may activate swallowing musculature and vagal nerve endings, promoting muscle contraction and enhancing brainstem-mediated swallowing reflexes to regulate deglutition (59).

This study incorporates significant methodological improvements over previous research, most notably through the inclusion of a healthy control group to establish baseline physiological parameters, enabling stronger mechanistic investigations and enhanced pathological characterization. By conducting the study at two centers while minimizing multi-center coordination challenges—including inter-site variability in equipment specifications, intervention protocols, and staff training standardization—we enhance methodological rigor. Despite the open-label design, this study incorporates multiple methodological safeguards to mitigate potential biases. Standardized assessments, third-party evaluators, and multimodal verification confined detection bias to an acceptable range. Performance bias was controlled by measuring baseline expectations with standardized scales and including these scores as covariates in efficacy analyses. Pre-specified subgroup analyses and thorough control of confounders minimized false-positive risks from data dredging while supporting evidence-based individualized care.

Our comprehensive efficacy evaluation employs multiple metrics: the Functional Oral Intake Scale (FOIS), fMRI-derived measures ReHo and ALFF, surface electromyography (sEMG), the Swallowing Disorders-Specific Quality of Life Questionnaire (SWAL-QOL), the National Institutes of Health Stroke Scale (NIHSS), Fiberoptic Endoscopic Evaluation of Swallowing (FEES) integrated with the Penetration-Aspiration Scale (PAS) and Yale Pharyngeal Residue Severity Rating Scale (YPR-SRS), and Patient-Reported Outcomes (PRO). Functional MRI (fMRI) serves as a superior non-invasive neuroimaging modality for dynamic neural activity monitoring (61), offering exceptional spatial resolution for mapping cerebral activation patterns across cortical and subcortical structures (thalamus, basal ganglia, cerebellum, and brainstem) (62). Crucially, fMRI captures data under near-physiological conditions, enabling investigation of spontaneous neuronal activity, functional connectivity networks, and neuroplastic changes (63). Previous research demonstrates an inverse correlation between ReHo values in swallowing-related brain regions and dysphagia severity in stroke patients (47), suggesting ReHo alterations may track neural compensation during swallowing recovery (48). Similarly, ALFF—quantifying spontaneous neural activity intensity (64)—shows treatment responsiveness (65). The SWAL-QOL is a validated assessment tool characterized by simplicity of administration, time efficiency, high reliability, and good validity (34). It provides quantitative measurement of swallowing-related quality of life, enabling clinicians to better evaluate patients’ swallowing function and dysphagia severity. The NIHSS employs standardized scoring criteria that ensure inter-rater reliability and comparability (48). Numerous studies have established the NIHSS as a simple yet effective predictive measure for neurological deficits (66–68), which can be used to forecast long-term functional recovery and guide rehabilitation planning. The objective observations from FEES are translated into quantifiable efficacy data using the Penetration-Aspiration Scale (PAS) and Yale Pharyngeal Residue Severity Rating Scale (YPR-SRS), thereby enhancing the precision of therapeutic outcome evaluation for the intervention. This study comprehensively evaluates acupuncture efficacy through four key dimensions: physiological function, cerebral activity, quality of life, and disease severity, thereby generating high-quality, internationally recognized evidence-based findings.

This study has several limitations that warrant consideration. First, the relatively small sample size may reduce statistical power, potentially limiting the generalizability of findings. Additionally, significant heterogeneity in intervention protocols made effective blinding challenging, increasing risks of performance and detection bias. Participant expectations and subjective perceptions may influence self-reported outcomes, potentially compromising the reliability of patient-reported measures. While objective clinical assessments provide valuable data, they remain susceptible to investigator interpretation bias. The follow-up in this trial will conclude at 60 days post-treatment to assess short-term efficacy. Should the primary outcomes prove positive, the research team will seek extended funding after study completion to conduct additional follow-ups at 6 and 12 months. These extended assessments will evaluate swallowing function, pneumonia incidence, and quality of life to determine the long-term durability of treatment effects.
